### Study arms

#### Experimental arm

After consenting, participants randomized to the experimental group will take a short online initial contact questionnaire to collect basic demographics. They will then view a 20-minute sleep health education video. Immediately after the presentation, the participant will be presented with a short sleep disorders risk assessment which displays the results upon completion, either high risk for a sleep disorder (obstructive sleep apnea, insomnia, or restless legs syndrome) or low/no risk a sleep disorder. Participants are then presented with a baseline questionnaire to assess sleep, health, and lifestyle. Finally, the experimental group participants will be invited to download the study app (“dayzz”). They will be encouraged to use the dayzz app throughout the study (up to 9 months, depending on date of enrollment).

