#### Control

Participants assigned to the waitlist control condition will, at baseline, complete the same initial contact and baseline questionnaires. Participants in the waitlist control group will complete the eDiary and monthly and end-of-study questionnaires. At the end of the study, waitlist control participants will receive the intervention (SHAW and dayzz app).

Each participant will also complete a daily electronic sleep diary (eDiary) sent via email for one week within the first month of enrollment and for one week within the third month of the study. For up to 9 months following the baseline procedure, on the 28th of each month, each participant will receive an email with a link to the monthly questionnaire. At the end of the study, each participant will receive a link to complete the end-of-study questionnaire. The eDiary and all questionnaires are completed online. This study was approved by the Partners HealthCare Institutional Review Board (IRB) on February 10, 2020 (Protocol #: 2019P003277). Please see the Fig 2 for a flow chart describing the study procedures. Per the IRB, a Data Safety Monitoring Board was not required for this clinical trial.

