#### Healthcare utilization

Healthcare utilization will be reported on monthly surveys. Participants will be asked to report interaction with the healthcare system, including visits to their primary care provider, emergency room, urgent care, or a specialist. They will further be asked to report any laboratory tests and diagnostic evaluations, including imaging, home sleep tests, and other examples of healthcare utilization. Healthcare costs will be estimated for each interaction through applying national average costs for each visit, test, and/or procedure.

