### Statistical plan

We plan to analyze anonymized data using an intention-to-treat approach (ITT). All outcome measures will be compared by assignment to the experimental and waitlist control groups in the primary analysis. The primary ITT analysis will include all participants who are randomized in the study. Secondary analyses will compare outcomes using an as-treated approach and an adherent to treatment approach. The as-treated approach will compare those who download dayzz to those who do not, regardless of their assigned randomization. We anticipate some cross-over between groups due to sharing of the app information among study participants. The adherent to treatment approach will exclude participants from the experimental group who did not engage with app throughout the study. We further plan to quantify temporal changes within participants assigned to the experimental group.

To evaluate changes in sleep behavior, we will examine the distribution of the data to determine if it meets assumptions for parametric tests. Assuming randomization has balanced known and unknown confounders and we observe a normal distribution, we will compare sleep duration between the groups using a t-test. We will use a rank sum test if the distribution is not normal. The distribution of the data will be examined, and transformations will be performed as necessary for valid comparisons. If potential confounders are not balanced between groups, we plan to use regression models with an appropriate link function and distribution to test all hypotheses. The number of healthy sleep changes at the end of the study will be compared between the groups using a rank sum test.

To evaluate changes in sleep quality, we will compare the proportion of participants with poor sleep quality according to the PSQI in the experimental group versus the waitlist control group using a chi-2 test. These continuous measures will be compared using a t-test. To examine changes in mood, alertness, and energy we will compare these ordinal variables using Wilcoxon rank sum tests between the experimental and waitlist control arms. We will estimate changes in absences and productivity using reported salary information and compare the cumulative cost of each using a t-test. We will estimate the incidence of crashes, near-crashes, and injuries which will then be compared using Poisson regression. Finally, we will compare cumulative healthcare costs over the study using t-tests.

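### Cumulative costs are t-tested without scaling to the months actually reported, and repeated safety counts are compared by Poisson regression with no named allowance for overdispersion

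*Protocol article*

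**What the plan says.** The Statistical plan fixes the economic comparisons. For absence and productivity: "We will estimate changes in absences and productivity using reported salary information and compare the cumulative cost of each using a t-test". For healthcare: "Finally, we will compare cumulative healthcare costs over the study using t-tests". For safety events: "We will estimate the incidence of crashes, near-crashes, and injuries which will then be compared using Poisson regression".

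Other sections show where the data come from:

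- Healthcare utilization: "Healthcare utilization will be reported on monthly surveys". Absence and performance also come from the monthly questionnaire, and so do crashes, near-crashes and injuries, where participants give the number of events in the past month.
- Control section, on the schedule for every participant: "For up to 9 months following the baseline procedure, on the 28th of each month, each participant will receive an email".
- Experimental arm section, on length of use: "up to 9 months, depending on date of enrollment".
- Recruitment and retention provides for up to two reminder emails to people who do not answer, so unanswered questionnaires are expected. No response rate is given.

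The primary analysis set is everyone randomized. The plan has two general safeguards: transformation when the distribution calls for it, and regression when confounders are unbalanced between arms.

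**The concern.** A cumulative total is interpretable as cost only if every participant is observed for the same time, or if the total is scaled to the time observed. Here the observed time is the number of monthly forms returned, which differs between people because of enrolment date and because of non-response. The first cause is independent of arm. The second need not be, since one arm is using an app and the other is waiting for it. Neither safeguard helps: a transformation changes the shape of the totals, and adjusting for confounders does not restore months that were never reported.

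The safety outcomes raise a different question. Near-crashes and injuries can recur in the same person month after month. A Poisson model takes the variance to equal the mean. If some people are much more prone to events than others, the variance is larger and the model's standard error is too small.

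The article's Discussion would treat improvement in employee and employer outcomes as strong evidence for the app, and the cost and safety results feed that statement.

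**Working it through.** The article gives no figure for this point: no response rate, cost distribution or event rate. Its only design figure, a detectable effect size of 0.16 with 500 per arm, does not enter the argument. Response rates, skewness, event rates and dispersions below are assumptions.

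**1. Distortion of a summed cost.** Let the mean cost per month be the same in both arms, and let unreported months add nothing. The expected total is (months of follow-up) × (response rate) × (monthly cost), so the ratio of totals, app to control, is the ratio of response rates.

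| Response, app v control | Ratio of totals | Apparent effect, none being true |
|---|---|---|
| 80% v 80% | 1.00 | none |
| 80% v 90% | 0.889 | 11% saving |
| 70% v 80% | 0.875 | 12.5% saving |
| 60% v 80% | 0.75 | 25% saving |
| 80% v 70% | 1.143 | 14% excess |

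The last row reverses the arms and shows that the distortion is not always a saving.

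**2. Effect on the t-test.** Null simulation: 500 per arm, 4 to 9 months of follow-up drawn equally in both arms, skewed monthly costs, 1,500 trials per row, nominal 5% level.

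| Response, app v control | Mean ratio of totals | Rejects: totals | Rejects: cost per reported month |
|---|---|---|---|
| 80% v 80% | 1.00 | 4.7% | 5.3% |
| 70% v 80% | 0.88 | 27% | 5.1% |
| 60% v 80% | 0.75 | 83% | 5.8% |

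The first row isolates unequal follow-up: no bias and a correct error rate. The last column was obtained with non-response unrelated to cost, and holds only then.

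**3. Overdispersion in the counts.** With variance/mean ratio φ, a Poisson test at nominal 5% has true type I error 2 × (1 − Φ(1.96/√φ)):

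- φ = 1.5: 1.96/1.225 = 1.60, giving 11%
- φ = 2: 1.96/1.414 = 1.39, giving 17%
- φ = 3: 1.96/1.732 = 1.13, giving 26%

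How large φ is depends on how common the event is. If individual event rates vary with relative variance v and the mean count over follow-up is μ, then φ = 1 + vμ, and the Poisson standard error is 1/√φ of the true one.

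| Mean count μ | v = 1 | v = 3 |
|---|---|---|
| 0.05 | 0.98 | 0.93 |
| 0.5 | 0.82 | 0.63 |
| 1 | 0.71 | 0.50 |

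Simulation with equal 80% response and a person-time offset already in the model (2,000 trials each, v = 1 to 3) gave 5–7% rejection at 0.01 events per month, 12–23% at 0.1, and 19–34% at 0.2. With the offset and a robust variance, rejection was 4–6% throughout, even at 70% against 80% response. Without the offset, that same response gap gave 32% rejection at 0.1 events per month with no overdispersion at all.

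**4. First recall window.** Forms go out on the 28th and ask about the last month. If enrolment is spread evenly over the month, on average half of the first window precedes randomization, a share of 0.5/m of all recall with m questionnaires. For m = 9 this is 5.6%; for an assumed m = 3 it is 17%. Taking a true rate ratio of 0.76, matching the 24% injury reduction cited in the Introduction, the observed ratio is 0.056 + 0.944 × 0.76 = 0.77, or 0.167 + 0.833 × 0.76 = 0.80. Both arms are affected alike, so this dilutes an effect and cannot create one.

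**The case against.** The article nowhere says that an unreturned month counts as zero. It may be imputed or pro-rated, and such rules often sit in an analysis plan that is not shown. This is fair, and it limits the finding: the distortion is conditional. What stands is that the comparison of cumulative totals by t-test is itself stated, and neither stated safeguard deals with missing months.

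Several stronger readings are tempting and are not supported:

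- *Unequal follow-up biases the costs.* It depends on enrolment date, which randomization balances between arms. It adds noise only.
- *The plan will manufacture savings.* That needs lower response in the app arm. Both arms get the same reminders and incentives, nothing says which will reply less, and if people with more events reply more the error can run the other way.
- *The 1.3 to 1 assignment weight proves differential loss in the cost data.* It implies relative retention of 1/1.3 = 0.77, hence a 23% apparent saving if randomized non-enrollees are kept at zero cost. But the weight concerns the enrolment steps and aims at equal enrolled groups. It says nothing about later monthly response, and the zero-cost rule is not in the text.
- *All the standard errors are too small.* The t-test estimates its variance from the data. The problem is confined to the Poisson models and is slight for rare crashes.
- *The Poisson model has no exposure term.* The plan speaks of incidence, which is compatible with a person-time denominator. An offset would not, however, deal with overdispersion.

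**Conclusion.** The point holds in a limited, conditional form. The stated cost analysis does not separate cost from the number of months reported. If missing months contribute nothing, each difference in response passes straight into the cost ratio: 12.5% for an assumed 70% against 80%, with a false-positive rate near 27% under the cost distribution simulated. With equal response and non-response unrelated to cost there is no bias. For counts, type I error of about 11% to 26% follows from assumed variance/mean ratios of 1.5 to 3. Such ratios are plausible only if near-crashes or injuries are fairly frequent; at a mean of 0.05 events per person the standard error is at most about 7% too small for the dispersions tried. The recall-window issue is minor and conservative. This is an inexpensive improvement to the stated methods, not evidence that the trial's results will be wrong.

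**What to change.** 1. **Costs.** Replace the t-test on totals with cost per reported person-month since randomization, or a generalized linear model for mean cost with a log link, offset log(reported months), and robust or bootstrap standard errors.
2. **Missing months.** State how they are treated, and add multiple imputation of missing months as a sensitivity analysis. This is needed because per-month scaling is unbiased only if non-response is unrelated to cost, and because people with no report have no per-month value although the primary set is everyone randomized.
3. **Crashes, near-crashes and injuries.** Use the same offset, with a robust (sandwich) variance or a negative binomial model.
4. **Optional.** Pro-rate the first questionnaire where its recall window starts before randomization.

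Only analysis wording and code change; data collection does not. The price is slightly wider intervals and, if item 4 is adopted, some loss of first-month information.

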## Discussion

Nearly 70% of Americans report routinely curtailing their sleep each month [1], and sleep disorders (affecting approximately 50–70 million) [3] are prevalent among US adults. Although strong evidence demonstrates that worksite-based sleep health education and sleep disorders screening and treatment can improve employee sleep and health, as well as workplace safety, productivity, and healthcare costs [6,7,10,11], such programs remain a minority of wellness initiatives reported by employers in the US [5].

Digital and mobile technologies, such as smartphone devices and wearable sleep and activity monitors, provide several benefits from the standpoint of workplace wellness. First, digital and mobile technologies often feature sensors that can track activities, such as sleep and exercise, and enable personalized messages based on the user and their unique needs [14,15]. Second, digital and smartphone technologies have the potential to reach employees outside the workday with health promotional messaging. Finally, digital and mobile tools may also be a cost-effective solution when viewed in comparison to high cost experts or coaches.

In this manuscript we describe an operational trial that aims to examine the sleep training smartphone app “dayzz.” The dayzz app offers a mHealth approach with personalized sleep training to improve sleep and address sleep issues. We will monitor participants for up to 9 months to examine the feasibility, acceptability, effectiveness and durability of the dayzz app for improving employee sleep and workplace outcomes in a large employer in the US Northeast. We intend to disseminate the findings by publishing the results in a peer-reviewed journal.

This clinical trial was originally scheduled to begin recruitment with a series of in-person events in March 2020. Our planned recruitment kickoff coincided with the date that the WHO declared COVID-19 a worldwide pandemic [21]. After this declaration from the WHO, our study team, like many other study teams [22], made the difficult decision to pause the planned recruitment efforts and re-imagined all aspects of it to be completely virtual including transitioning the SHAW program from in-person to a video format. After successfully transitioning all study policies and procedures, we launched the trial in August 2020.

This randomized trial tests whether the dayzz app is effective in improving sleep, health and well-being of employees. Improvements in employee and employer outcomes observed in this trial would offer strong evidence that, despite the stressors of the current pandemic environment, a smartphone-based solution may be effective for improving sleep and workplace outcomes. A smartphone-based approach to improve sleep and sleep disorders has the potential to be a viable strategy for improving employee health, safety, and well-being. Results of this trial will indicate whether dayzz is a feasible, acceptable and effective approach as an employer-based sleep training and sleep disorder care program.

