## Abstract

Sleep deficiency is a hidden cost of our 24–7 society, with 70% of adults in the US admitting that they routinely obtain insufficient sleep. Further, it is estimated that 50–70 million adults in the US have a sleep disorder. Undiagnosed and untreated sleep disorders are associated with diminished health for the individual and increased costs for the employer. Research has shown that adverse impacts on employees and employers can be mitigated through sleep health education and sleep disorder screening and treatment programs. Smartphone applications (app) are increasingly commonplace and represent promising, scalable modalities for such programs. The dayzz app is a personalized sleep training program that incorporates assessment of sleep disorders and offers a personalized comprehensive sleep improvement solution. Using a sample of day workers affiliated with a large institution of higher education, we will conduct a single-site, parallel-group, randomized, waitlist control trial. Participants will be randomly assigned to either use the dayzz app throughout the study or receive the dayzz app at the end of the study. We will collect data on feasibility and acceptability of the dayzz app; employee sleep, including sleep behavioral changes, sleep duration, regularity, and quality; employee presenteeism, absenteeism, and performance; employee mood; adverse and safety outcomes; and healthcare utilization on a monthly basis throughout the study, as well as collect more granular daily data from the employee during pre-specified intervals. Our results will illuminate whether a personalized smartphone app is a viable approach for improving employee sleep, health, and productivity.

**Trial registration**: ClinicalTrials.gov Identifier: NCT04224285.

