Research has shown that workplace health programs focused on employee sleep or sleep disorders screening are effective for improving employee sleep, health, well-being, and workplace outcomes. In a randomized controlled trial of an in-person sleep education and sleep disorders screening intervention, researchers found there was a 24% reduction in injuries and a 46% reduction in disability day usage over the following year [10]. In a national trucking company, each employee diagnosed and treated for sleep apnea through an employer-sponsored program, saved nearly $3,000 per employee in health care costs annually [11].

In part catalyzed by the COVID-19 pandemic, there has been a widespread adoption of flexible and work-from-home policies among employers [12], and many forecast that worksites are likely to feature these policies when employees return to work [13]. These trends present new challenges to employee health and wellbeing when employees manage both work and personal obligations inside the home. The trend toward increased work-from-home policies and flexible work schedules may also presents opportunities for digital health programs for improving employee health. Digital platforms, such as websites, virtual coaching, and smartphone applications, may extend sleep health and wellness programs and offer tangible benefits to employers, such as scalability and cost effectiveness. These digital and mobile health (mHealth) approaches are particularly promising as they have the ability to monitor user behavior (e.g., time spent sleeping or number of steps taken) and to personalize messages tailored to a user’s lifestyle and needs [14,15], aimed at nudging towards health promoting behaviors and attitudes.

The purpose of this study is to conduct a randomized controlled trial to evaluate a smartphone app designed to improve employee sleep health and improve workplace outcomes. We will ascertain the feasibility and acceptability of the smartphone app and determine whether use of the app will improve sleep, health, mood, productivity, safety, and productivity among a large employee population in the US Northeast.

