## Materials and methods

### Study design

We will conduct a single-site, randomized, two-arm, parallel-group controlled trial using a waitlist control design. We will enroll a target of 1,000 daytime employees into the study, 500 randomly assigned to the experimental group and 500 to the control group. The experimental group will receive access to the dayzz app as well as to a short sleep health and wellness (SHAW) education program, developed by the Sleep Matters Initiative which includes screening for common sleep disorders. The control group will receive the dayzz app and SHAW at the end of the study. The study recruitment was originally intended to be conducted in-person. However, due to the onset of the COVID-19 pandemic at the start of study implementation, the study recruitment, enrollment, and follow-up procedures were re-designed to be completed entirely online. Please see the Fig 1 for a flowchart of enrollment, interventions, and assessments.

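### The randomised contrast is SHAW education and screening plus dayzz against waitlist, but the abstract, aim and discussion present it as a test of the dayzz app

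*Protocol article*

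**What the plan says.** All references are to the Protocol article.

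**What the arms receive.** Study design: "The experimental group will receive access to the dayzz app as well as to a short sleep health and wellness (SHAW) education program", a programme "which includes screening for common sleep disorders". The Experimental arm section gives the order of events. After a short initial questionnaire, "They will then view a 20-minute sleep health education video". Next, "the participant will be presented with a short sleep disorders risk assessment which displays the results upon completion". A baseline questionnaire follows, and only then the invitation to download dayzz. Under Control, waitlist participants "complete the same initial contact and baseline questionnaires", then the eDiary and the monthly and end-of-study questionnaires. They receive SHAW and dayzz when the study ends, and that section names these two together as the intervention.

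**What the trial is said to test.** The Abstract never mentions SHAW: "Participants will be randomly assigned to either use the dayzz app throughout the study or receive the dayzz app at the end of the study". The aim at the end of the Introduction is whether use of the app improves sleep, health, mood, safety and productivity. The Discussion speaks of the effectiveness of dayzz, states that "This randomized trial tests whether the dayzz app is effective in improving sleep, health and well-being of employees", and closes by saying that the results will indicate whether dayzz is effective.

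**What will be compared.** The Statistical plan makes the primary analysis intention-to-treat by assigned arm. Secondary analyses are as-treated (dayzz downloaders against non-downloaders, whatever their assignment) and adherent-to-treatment (dropping experimental participants who did not engage with the app).

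**The concern.** Two things change together at randomisation: SHAW and the app. A difference between the arms could come from either or from both, and the comparison cannot tell these apart. If the results are reported in the terms the Abstract and Discussion use, an employer would read a package effect as evidence for the app. An employer deciding whether to buy the app, or to offer only a short video and a screening questionnaire, would be deciding on something the trial did not test.

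The worry is not abstract, because the article itself treats education and screening as potentially effective. In the in-person programme cited in the Introduction, "researchers found there was a 24% reduction in injuries and a 46% reduction in disability day usage over the following year". Injuries and disability days are also collected here. The Discussion calls the evidence for worksite sleep education and sleep disorder screening and treatment strong.

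**Working it through.** **1. Components by arm during follow-up**

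| Component | Experimental | Waitlist control | Section |
|---|---|---|---|
| Questionnaires and eDiary | yes | yes | Control |
| SHAW video, 20 minutes | yes | no (end of study) | Experimental arm; Study design |
| Risk assessment with result shown | yes | no (end of study) | Experimental arm; Study design |
| dayzz | yes | no (end of study) | Experimental arm; Control |

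The last three rows differ between the arms. If S is the mean effect of SHAW without the app and A the mean further effect of adding the app to SHAW, the intention-to-treat contrast estimates S + A. No arm receives SHAW without the app, so A cannot be separated from S.

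**2. Whether another planned analysis isolates A**

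- *As-treated.* Not randomised. SHAW precedes the download step, so most downloaders will have been offered SHAW. The non-downloaders mix experimental participants who had SHAW with controls who did not.
- *Adherent-to-treatment.* Still package against waitlist, now with selection on engagement in one arm only.
- *Change over time within the experimental arm.* No comparator, and both components are delivered from the start.

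None identifies A.

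**3. Could the primary test succeed with no app effect?**

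Inputs from Power analysis: 500 per arm, detectable standardised effect 0.16. Significance level, sidedness and power are not stated there, so 5% is an assumption and both sidednesses are shown. Normal approximation, SD 1, equal arms.

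SE = √(2/500) = 0.0632.

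Reproducing the plan's figure at 80% power:
- one-sided: (1.645 + 0.842) × 0.0632 = 0.157, which rounds to the stated 0.16
- two-sided: (1.960 + 0.842) × 0.0632 = 0.177

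Now set S = 0.16 and A = 0. The package contrast is still 0.16, and 0.16/0.0632 = 2.530:
- two-sided: Φ(2.530 − 1.960) = Φ(0.570) = 71.6%
- one-sided: Φ(2.530 − 1.645) = Φ(0.885) = 81.2%

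A completely inert app would still go with a significant result in about 72% (two-sided) or 81% (one-sided) of trials. A larger sample raises these figures and does nothing to separate S from A.

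**4. What an app-only contrast would look like**

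If both arms had SHAW, the target would be A alone. For assumed SHAW shares of a total effect of 0.16, two-sided 5%:

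| SHAW share | A | Power, 500 per arm | n per arm for 80% power |
|---|---|---|---|
| 25% | 0.12 | 47.5% | 1091 |
| 50% | 0.08 | 24.4% | 2453 |
| 75% | 0.04 | 9.2% | 9812 |

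Power is Φ(A/0.0632 − 1.960); n is 2 × (2.802/A)², rounded up. The shares are illustrative; the article gives no basis for choosing among them.

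**The case against.** The strongest reply is that nothing is hidden. Study design says that SHAW comes with the app, the Control section defines the intervention as both, and testing a package against waitlist is a legitimate choice in an operational trial. The primary analysis is a valid test of that package. All of this stands. It locates the fault in the stated inference and not in the design or the analysis. It does not excuse the Abstract, aim and Discussion, which a reader may see without the Methods and which name only the app. Nor is this a detail left to a fuller document, since the conflict lies between statements the article makes.

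Several stronger readings are tempting and are not supported:

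- *The article already claims that dayzz works.* It does not. The Discussion is prospective and partly hedged, and there are no results to withdraw.
- *Controls receive nothing.* They receive no intervention component during follow-up, but they complete the same baseline questionnaires, the monthly questionnaires and the eDiary, and get both components at the end.
- *The 24% and 46% reductions measure what SHAW would do here.* They come from an in-person programme, whereas SHAW was converted to a video. They make an effect of SHAW plausible and say nothing of its size.
- *Education and screening belong to SHAW alone.* dayzz has its own sleep-disorder questionnaire, sleep hygiene modules and a sleep apnoea referral module. An effect working through education or screening could therefore come by either route. The overlap makes attribution harder, not easier.

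**Conclusion.** The point holds as one of attribution. The randomised comparison identifies the effect of SHAW plus dayzz against waitlist. It does not identify the effect of dayzz, which is what the Abstract, aim and Discussion say the trial tests and will indicate. No other planned analysis supplies it.

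The app's share of any observed effect is simply not estimable from this design. The 72% figure (81% one-sided) shows the consequence in one extreme case, and rests on an assumed 5% level, an assumed SHAW effect equal to the planned 0.16, and no app effect. It is not a forecast. The conclusion itself needs none of these assumptions and follows from the description of the arms.

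A reader might go further and infer that the trial is uninformative or its primary analysis invalid. The article does not support that: the package effect is a useful quantity and the intention-to-treat contrast targets it.

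**What to change.** 1. In the Abstract, the aim and the Discussion, state the comparison as SHAW (education video and sleep-disorder risk assessment) plus dayzz against waitlist, following the definition already in the Control section. Word the planned conclusions to match, and carry the same wording into the results report.
2. Add one sentence saying that the separate effect of the app is not identified by this design.
3. In the Statistical plan, describe the as-treated comparison as exploratory and say that it does not estimate an app-only effect. The adherent-to-treatment comparison needs the same caution.

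This is wording only. No data collection, analysis or sample size changes. The cost is a narrower headline claim.

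Giving SHAW to both arms is not recommended as a way to rescue an app-only claim. The Discussion says that the trial launched in August 2020, so the change would mix two control conditions within one arm. It would also shrink the contrast: under the assumed shares above, two-sided power with 500 per arm would be 47.5% at best and 9.2% at worst.
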